|--------|-------------------------------------------------------------------------------------------------------------------------------------------------------------------------------------------------------------------------------------------------------------------------------------------------------------------------------------------------------------------------------------------------------------------------------------|--------|---------------------------|---------------------|--------------------------------------|----------|-------------------------------------------------------------------------------------------------------------------------------------------------------------------------------------------------------------------|
|        | 
(b) information provided to carers and the resources to which they were referred,
 
(c) the extent to which carers engaged with resources
 
(d) any safety concerns identified by the FECH nurse and how these were managed; and
 
(e) time taken to implement processes.
 
Also recorded will be contextual factors that may be barriers to, or facilitators of, the effectiveness of the FECH program.
 |        | dose of the intervention. |                     | research drive at Curtin University. |          | Any electronic data not in REDCap will be transferred as necessary for analysis and storage via the secure upload and download systems of Curtin and Griffith Universities so that all data transfers are secure. |

The following paragraphs complete our data management plan.

The relevant *policies and procedures* taken into account when developing our data management plans include those of the health services, Universities, and the DHS (now Services Australia). Importantly, University regulations dictate data storage for 25 years from the publication of results from a clinical trial. However, health department data and qualitative data are required to be destroyed in accordance with the NHMRC guideline of 7 years from the publication of results.

When considering *contractual and licensing arrangements and confidentiality agreements*, we recognise the agreements that are often required for the use of questionnaires/tools (including the CSNAT tool). Agreements will be put in place, as required, by the Research Office at Curtin (ROC) and/or Griffith University (as required). Confidentiality agreements are entered into by all investigators and research staff as they join the project, via the Research Governance System of WA Health.

Project staff will all undergo *training* for their roles in the project, as appropriate. For example, the FECH Nurses will all undertake a three-day training course in Perth prior to commencing their roles. The research staff employed to recruit study participants and collect data (POs) will be provided with the necessary training by the relevant state-based investigators. Any new employees replacing others during the study will also be trained as appropriate.

*Information from the data management plan that needs to be communicated to potential participants* includes what data they will be asked to contribute and how, what data about them will be accessed from elsewhere, and what will happen to these data (including how it will be shared, stored, used, and destroyed). Therefore, these issues are explained in our study information sheets.

*Risk management* has been carefully considered as we have developed our data management plans informed by NHMRC guidelines. Additional steps, not previously detailed, include:

- (a) reducing the risk of error via frequent checks of data entry conducted by the State Project Managers;
- (b) applications for data approved by custodians of the administrative data that ensure these data, when used by the researchers for data analyses, are non-identifiable (following principles of separation of identifiable linkage data and non-identifiable service data); and
- (c) the completion of project staff training in the research module addressing good clinical practice whenever these staff are involved with recruitment, data collection, or data management.

Regarding data storage, the data sets containing de-identified administrative data will reside only on a password protected drive (the secure Research Drive at Curtin University) in a project specific password protected folder. Access to this folder will be restricted to researchers involved in the project who are subject to the appropriate confidentiality agreement and have been granted access by the CPI. Access to the research drive is limited to Curtin University staff and research students and data on this drive are protected via the Curtin firewall, antivirus software, and automatic backups. All computers used for access to these data will have the screen lock set at 5 minutes of inactivity and will be password protected.

After data collection has ceased, all remaining data sets will be stored in a separate folder on the same secure research drive. Access to this folder will also be restricted to researchers involved in the project who are subject to the appropriate confidentiality agreement and who have been granted access by the CPI. However, access may be made available to additional research staff to those eligible to access the administrative data.

During data collection, the data collected via REDCap will be stored in the secure CTDMC environment (see Table 3 for access details). *Table 3 also addresses data archiving and destruction.*

### *Statistical Analysis*

**Statistical analysis for effectiveness** will be led by CI [name] and AI [name], biostatisticians. In our preliminary work, there was <20% missing data. Because it is difficult to establish if data are missing completely at random (MCAR), partially missing at random (MAR), or not MAR, we will use Multiple Imputation (MI) methods informed by a sensitivity analysis to manage this, creating 25 or more data sets. Two analyses will be performed, namely: an analysis using only the observed data, and secondly, after missing value substitution, where necessary. Data will be analysed using an 'intention-to-treat' (ITT) approach. Secondary outcomes will be analysed in a similar manner to the primary outcome. Statistical analyses will be conducted using SAS version 9.2 software and a p-value <0.05 will be taken to indicate a statistically significant associations/differences in all tests.

Descriptive statistics will summarise the profile of study participants. These will be presented as frequencies and percentages for categorical variables; means, standard deviations, medians and ranges for variables measured on a continuous scale. Differences in these demographic and baseline health status variables between groups at baseline will be compared using Chi-square, t-tests or non-parametric Wilcoxon 2-sample tests as appropriate. Changes from baseline in the AQoL-8D score for the carer will be calculated to each time point and tested for normality using the Shapiro-Wilk statistic; if not normally distributed, a Box-Cox transformation will be applied to the measure before further analysis. Comparison of the changes in AQoL-8D scores between control and intervention groups will be performed using a mixed model (regression model with the carer group identified as a random effect). This model takes into account correlation between repeated measurements on each individual. An interaction term between time and group will be introduced into the model to test whether rates of change in the outcome differ between groups. If differences between the groups are evident at baseline, these will be included in the model as covariates so that adjustment can be made before examining differences between groups in outcomes.

**Preparation for economic analyses.** As noted above, carer health state utilities will be captured at baseline and for the previous 12 months for all carer participants who meet the inclusion criteria, and at 3, 6, and 12 months post recruitment. The AQoL-8D (13, 14) utility algorithm weighted for the Australian population will be used to derive an overall index of the health state utility at each time point. The QALY profile for each carer will be calculated using area under the curve methods.

**Cost utility and cost effectiveness analyses.** These analyses will be led by CI [name], a highly experienced health economist and will evaluate all outcomes that show a significant difference across the arms of the trial. Cost effectiveness of the intervention will be measured using the

framework of a within trial cost utility analysis. An incremental cost-utility analysis will be undertaken to compare the mean incremental cost and quality adjusted life year (QALY) profiles for each group according to intervention status. We will also estimate cost effectiveness utilising measurement of the change in other secondary outcomes where a significant difference is observed between the intervention and control groups. Confidence intervals will be presented around the incremental cost effectiveness ratios (ICER), and cost effectiveness acceptability curves for varying threshold values of cost effectiveness will be presented. A 12-month time horizon will be used and a health system perspective using within trial probabilities and costs will be undertaken. Assessment of the sensitivity of the results obtained to variation in measured effectiveness, health care resource use, intervention and usual care unit costs and participant subgroups will be undertaken using one-way and probabilistic sensitivity analysis, as per best practice guidelines (51).

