In addition, hospital usage by care recipients in the follow-up period was (non-significantly) lower for older people whose carers received the FECH program, compared with controls (28). However, this preliminary work was in one setting, the program needed to be extremely brief, the study was only powered to detect changes in caregiving preparedness, and patient and carer follow-up periods were short. The current study will examine impacts from a 6-month version of the FECH program, designed to further embed the problem-solving approach for carers; it will provide more generalisable findings; be powered to detect clinically important changes in carer, care recipient, health system, and cost outcomes; and examine change over substantially longer periods. Both cost utility analyses and effectiveness analyses will examine caregiving sustainability as an outcome.

In summary, a critical challenge facing Australia is the need to ensure that the rapidly increasing population of older people may remain at home for as long as they and their carers desire, while minimising risks to carer health. Meeting this challenge will have substantial benefits for Australian society as a whole. Our study will determine the extent to which the FECH program can help to meet this challenge. Findings will provide robust evidence, which, if outcomes are positive, can underpin changes in practice and policy in metropolitan Australia and inform similar initiatives elsewhere.

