## **Aims and Hypothesis**

*Aims of this trial are to:*

- (1) Measure impacts from participation in the FECH program on the HRQoL of carers of older people discharged home from hospital (**primary aim**).

- (2) Measure impacts from participation in the FECH program on (a) other carer outcomes (preparedness to care, self-efficacy, strain, distress, use of health services, use of medications), (b) patient outcomes (symptom distress, level of independence, use of health and residential care services, use of medicines), and (c) costs for health services, medicines, and residential care.
- (3) Explore and describe how caregiving is influenced by the program.

*Hypotheses are that:*

- (1) Carers participating in the FECH program in addition to receiving usual hospital discharge support, when compared with carers receiving usual discharge support alone, will (during the program and for the following 6 months):
  - a) report improved HRQoL, - better self-rated physical and/or psycho-social health expressed as improved AQoL-8D scores (29, 30) (**primary hypothesis**);
  - b) report improved caregiving preparedness (higher scores on the Preparedness for Caregiving Scale [PCS] (31)), decreased carer strain and distress (lower strain and distress scores on the Family Appraisal of Caregiving Questionnaire-Palliative Care [FACQ] (32)), and improved caregiving self-efficacy (higher scores on the Caregiver Inventory [CGI] (33)); and
  - c) experience decreased emergency presentations to hospital, days in hospital, ambulance trips, and use of primary health services/medications for their own health problems (from health system data and carer reports).
- (2) The FECH program will be cost effective for carers, defined as having an incremental cost-effectiveness ratio of less than AUD\$50,000/QALY gained.
- (3) Older people whose carers participate in the FECH program in addition to receiving usual discharge support, when compared with older people whose carers receive usual discharge support alone, will experience (during the program and for the following 6 months):
  - a) decreased symptom distress (lower scores on Symptom Assessment Scale (SAS) (34)); improved independence (higher scores on Barthel Activities of Daily Living Index (BADLI) (35)); and

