  - b) delayed permanent admissions into RACFs (from carer reports), plus fewer emergency presentations to hospital, days in hospital, and ambulance trips, also decreased medication use and use of primary health services (from health system data), resulting in overall decreased costs to the health and residential aged care systems.

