## **Project Design**

### *Methodological Approach*

The proposed single-blind, multi-centre, RCT (n=648 dyads after estimated attrition of 30%) will evaluate the effect of providing usual discharge support plus the FECH program on carers' HRQoL compared to providing usual discharge support alone. This design, with assessors blinded to the group assignment of study participants, has been chosen to ensure that the strongest possible evidence will be obtained to either support or refute the study hypotheses. The study also directly compares outcomes from usual care to those from usual care plus the FECH program in terms of carer outcomes directly addressed by that program (preparedness to care, carer self-efficacy, carer strain, and carer distress). Further outcomes for carers, care recipients, the health and residential care systems, and related costs, will also be evaluated.

A 1-year follow-up period for carers will facilitate accurate determination of Quality Adjusted Life Years (QALYs), required for cost utility analyses. This timeline also allows for the lag time occurring when using linked data for follow up of carers and care recipients (time for data to enter the 'system' and queuing for data extraction).

Qualitative data from carers will explore and describe carers' experiences of the FECH program in the short and long term, particularly how the program influences caregiving. Process evaluation will be concurrent with FECH program administration.

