### *Power Calculations*

The primary outcome is the change in total score on the AQoL-8D (13, 14) for the carer. Hawthorne and Osborne (37) consider that a very small effect size of 0.06 may be of clinical

---

 The GCH Nurse Navigator is an advanced practitioner within an interdisciplinary team who works closely with the patient and their family to provide continuity of care both across acute and community care

importance in relation to this instrument. However, we anticipate a larger effect size, based upon:

- (a) our assessment of changes in health, measured using the SF12 (38) during our preliminary study (9), in which we obtained positive change (effect sizes) from baseline until immediately post-intervention in physical health (0.17) and mental health (0.22);
- (b) that the AQoL-8D is a more appropriate outcome measure than the SF-12 for this study as psychosocial components of health are emphasised more; and
- (c) that we are now implementing an expanded intervention with longer follow up.

Therefore, we designed this study with 80% power to detect an effect size of 0.22. This would require 324 carer dyads in each of the study arms (control and intervention), determined using the G\*Power sample size calculator (39).

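### A blanket p<0.05 rule for about 18 unordered secondary comparisons gives a 22% to 60% chance of a false secondary result (assumed correlation 0.8 to 0), and such a result can select economic analyses

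*Protocol*

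**What the plan says.** Protocol, Statistical Analysis, sets one threshold for everything: "a p-value <0.05 will be taken to indicate a statistically significant associations/differences in all tests". It adds: "Secondary outcomes will be analysed in a similar manner to the primary outcome".

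The primary is clear. Power Calculations states: "The primary outcome is the change in total score on the AQoL-8D". Aims and Hypothesis marks only 1a as the primary hypothesis.

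The remaining outcomes in Aims and Hypothesis are also numbered hypotheses, each predicting benefit. Under 1b, carers are to "report improved caregiving preparedness" and show "decreased carer strain and distress (lower strain and distress scores" on the FACQ, plus better self-efficacy. Hypothesis 1c covers the carer's own service and medication use. Hypothesis 3a covers patient symptom distress and independence. Hypothesis 3b begins with "delayed permanent admissions into RACFs (from carer reports), plus fewer emergency presentations to hospital, days in hospital, and ambulance trips" and goes on to medication, primary care and overall cost. Hypothesis 2 is different in kind: it is met if the incremental cost-effectiveness ratio is below AUD$50,000 per QALY.

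Two other sections bear on how the results will be read. Methodological Approach says the design was chosen so that "the strongest possible evidence will be obtained to either support or refute the study hypotheses". Rationale for the Study says: "Findings will provide robust evidence, which, if outcomes are positive, can underpin changes in practice and policy".

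The paragraph on cost utility and cost effectiveness, also in Statistical Analysis, ties the economic work to outcomes on which the arms differ significantly, secondary outcomes included.

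**The concern.** The protocol states a rule here; it does not simply leave the matter open. An analysis plan that ordered or adjusted the secondary outcomes would have to override the instruction that p<0.05 is significant in every test. As written, any of about 18 secondary comparisons can be called significant, and hence a supported hypothesis, whatever the primary shows.

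Two things are at stake. One is the reading of the secondary results if the AQoL-8D comparison is null. The other is that a significant secondary result has a practical consequence: it decides which further cost-effectiveness analyses are done. A chance finding would therefore receive an economic evaluation that the other outcomes do not, and could enter the case for implementation.

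**Working it through.** **The plan's own figure.** Power Calculations gives 324 dyads per arm for 80% power at an effect size of 0.22. The usual formula gives n = 2 × (1.960 + 0.842)² / 0.22² = 2 × 7.85 / 0.0484 ≈ 324.4, or 325 rounded up. Power at 324 per arm is 79.96%. Allowing for 30% attrition, 648 / 0.70 ≈ 926, against the stated 925. The figures reproduce with a two-sided 5% test; a one-sided test would need about 256 per arm. Sidedness is not stated, so two-sided testing is assumed below on this basis.

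**Counting the secondary family (Aims and Hypothesis).**
- 1b: preparedness, strain, distress, self-efficacy = 4
- 1c: emergency presentations, hospital days, ambulance trips, primary care, medications = 5
- 3a: symptom distress, independence = 2
- 3b: residential care entry, emergency presentations, hospital days, ambulance trips, medications, primary care, overall cost = 7

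Total: 4 + 5 + 2 + 7 = 18. Hypothesis 2 is left out because it is not a p-value test.

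**Chance of at least one p<0.05 if the program has no effect.** For independent tests:
- either direction: 1 − 0.95^18 = 0.603
- in the program's favour only: 1 − 0.975^18 = 0.366

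For correlated tests, normal test statistics with a common pairwise correlation were integrated numerically. The protocol gives no correlations, so a range is shown.

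| Assumed correlation | Either direction | In the program's favour |
|---|---|---|
| 0 | 0.603 | 0.366 |
| 0.3 | 0.509 | 0.263 |
| 0.5 | 0.398 | 0.199 |
| 0.7 | 0.277 | 0.139 |
| 0.8 | 0.216 | 0.108 |

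**Sensitivity to the correlation pattern.** A single correlation across carer scales, patient scales and two people's service use is a simplification. With four blocks (4, 5, 2 and 7 outcomes), simulation gives:
- within-block 0.3, between-block 0: 0.57 in either direction, 0.33 favourable
- within-block 0.5, between-block 0 to 0.2: 0.52 to 0.49, and 0.29 to 0.26
- within-block 0.7, between-block 0 to 0.2: 0.44 to 0.42, and 0.24 to 0.22

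**Sensitivity to the count.** If primary care and medications in 1c are one outcome, 17 tests remain: 0.582 at correlation 0 and 0.212 at 0.8. If overall cost is also dropped, 16 independent tests give 1 − 0.95^16 = 0.560. The result does not turn on the exact count.

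Repeated follow-ups, and the paired observed-data and imputed analyses, are not counted. They would raise the rate only if each were read separately.

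**The case against.** The strongest reply is that this is ordinary practice. One primary outcome is named, the others are called secondary, and adjustment among secondaries is commonly left to the analysis plan. The p<0.05 sentence sets a per-test level and promises nothing about the family. Much of this stands. The primary's error rate is untouched, and the missing order is only within the secondary tier. It is not fair to set a family rate against 5% as if the protocol had promised the latter. What does not stand is that the point can simply wait for the analysis plan, because the protocol has already fixed the rule for all tests and made significance a trigger for further analysis.

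Several stronger readings are tempting, and the documents do not support them.

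- A reader might quote a flat 40%. That needs a common correlation of 0.5 among all 18 outcomes, which no section gives. The figure also counts results against the program.
- A reader might infer that a false claim of benefit is likely by chance alone. The favourable-direction range is 11% to 37%, below one half throughout.
- A reader might say that every secondary hypothesis is affected. Hypothesis 2 is decided by a cost-per-QALY threshold.
- A reader might take the protocol to say that one significant secondary outcome would carry a policy claim after a null primary. It does not. The sentence on supporting or refuting hypotheses explains the blinded design and follows one about carers' HRQoL; the policy sentence says only what positive findings could underpin. The protocol permits that use without announcing it.
- A reader might count a separate test at each follow-up. The analysis described is a mixed model with a time-by-group interaction.

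**Conclusion.** The point holds for the secondary tier. About 18 directional comparisons share an unqualified 5% rule with no order, adjustment or supportive status. If the program has no effect, the chance of at least one nominally significant secondary result is about 22% to 60%, and about 11% to 37% for one in its favour. These figures assume two-sided tests, normal test statistics, no effect on any outcome, and a common correlation from 0.8 down to 0; the block models fall inside both ranges. The consequence is concrete because significance selects further cost-effectiveness analyses. The primary AQoL-8D comparison is not weakened. This should be changed, but it does not threaten the trial's main conclusion.

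**What to change.** Make two wording changes, both in Statistical Analysis.

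1. Replace the sentence on p-values with text to this effect: *The two-sided 5% level applies to the primary comparison of carer AQoL-8D. Hypotheses 1b, 1c, 3a and 3b are secondary and supportive. They will be reported as estimates with 95% confidence intervals, and no single secondary p-value will on its own be taken to support a hypothesis or a claim of effectiveness.*
2. In the cost utility and cost effectiveness paragraph, replace the significance trigger with a list of outcomes fixed in advance. Changing only the first sentence would leave the trigger in place without a defined threshold.

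Neither change needs more data or participants. The cost is that an isolated secondary p<0.05 can no longer be presented as a supported hypothesis.

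A formal secondary procedure is optional and not part of this fix. One choice is Holm's method on the four carer outcomes in 1b, tested only if the primary is significant. Its power must then allow for that gate. With 80% power for the primary at 0.22, no gated secondary can exceed about 80%. For distress, using the pilot effect of 0.269 (Rationale for the Study) with 324 per arm and Holm's strictest level, 0.05 / 4 = 0.0125, power before the gate is 0.82. If distress is independent of the primary, gated power is 0.82 × 0.80 ≈ 0.66. Without gate or adjustment it is about 0.93. No pilot effect is given for self-efficacy, so its power cannot be stated.

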### *Recruitment*

Our recruitment target is 925 dyads to accommodate anticipated attrition of 30% and achieve the final sample of 648 dyads. Recruitment, baseline assessments, and outcome assessments will be undertaken by a team of Project Officers (POs).

**Identifying potential participants.** As in our preliminary study, POs will liaise with the ward staff to identify carer-patient dyads that might meet study inclusion criteria. The following approaches will provide information to the staff working in the areas where study recruitment will be undertaken and/or to potential patient and carer study participants:

1. Articles explaining study plans/progress in hospital staff newsletters.
2. Articles explaining the study in external organisations' newsletters provided to carers, such as those distributed by Alzheimer's WA or Carers WA.
3. Oral presentations at staff meetings and Multi-Disciplinary Team (MDT) forums when recruitment is about to commence and when it is finished – with updates as necessary to ensure that all the relevant staff remain aware of the study activity.
4. Information about the study on posters displayed in the participating wards.
5. At SCGH, subject to hospital approval, slides will be uploaded onto the hospital TV to explain the study and provide details of how to contact the study team.
6. Flyers will also be provided to all participating wards. These flyers will briefly describe the study and who might be eligible to take part. The ward staff (nurses, allied health staff, doctors) will be asked to distribute these flyers to patients and/or families that might meet study inclusion criteria, and they will also be available for the research team to hand out when explaining the study. The flyers will have a contact number for queries and a tear off slip that the patient or family member can complete with contact details if they would like to know more about the study. Boxes will be placed on the wards so that these slips

can be dropped into them and the research staff will follow up on requests for information on a daily basis. Subject to the agreement of the hospitals, a flyer will also be placed into each discharge envelope of an older patient returning home, in case they have not yet had an opportunity to learn about the study.

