#### *Database Setup, Random Assignment, and Blinding*

The Clinical Trials and Data Management Centre (CTDMC) at Curtin University will manage database set up and randomisation processes to ensure the integrity of these processes and of blinding. We will use stratified randomisation so that numbers of participating dyads in the control and intervention groups will be balanced within each hospital. A list of treatment allocations will be prepared before the study; it will contain a study number (whole number, starting from one), and a code to indicate the group (intervention or control). The list will be generated by the CTDMC using computer-generated random numbers, organised so that recruitment to the two study arms occurs at an approximately equal rate. This will be done using a blocking strategy, with half of the numbers within each block allocated to each treatment. Block length will be randomly selected and comprise an even number (from 6-12). This means that, at the end of each block, there will be an even number of dyads allocated to each group (control/intervention). A list of case numbers will be provided to each hospital so that the next dyad to be recruited within the hospital can be assigned the number at that time.

The treatment allocation list will be stored as a password protected file on R drive at Curtin University and will only be accessible to the trial's CTDMC REDCap administrators and any investigators or study staff specifically designated as requiring access for study oversight purposes. The executive officer from the CTDMC will be responsible for setting up this folder and will need to approve access for anyone else. To maintain blinding to group allocation, no investigators or study staff who are involved in recruitment, obtaining baseline data, obtaining outcome data, or analysis of these data will be allowed access.

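### The primary AQoL-8D model chooses covariates by observed baseline difference and does not fix baseline AQoL-8D in advance, so a valid comparison gives up precision.

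*Protocol*

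**What the plan says.** Under Power Calculations, "The primary outcome is the change in total score on the AQoL-8D" for the carer, and "we designed this study with 80% power to detect an effect size of 0.22", which the protocol puts at 324 dyads per arm.

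Under Statistical Analysis three steps follow one another:

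- Baseline tests: "Differences in these demographic and baseline health status variables between groups at baseline will be compared using Chi-square, t-tests", or Wilcoxon tests where suitable.
- Primary comparison: changes from baseline in AQoL-8D are compared between arms in a mixed model for repeated measurements, with a time-by-group interaction added.
- Covariates: "If differences between the groups are evident at baseline, these will be included in the model as covariates".

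No threshold defines when a difference counts as evident, and no covariate is named in advance. Secondary outcomes are to be handled in a similar way, so the rule extends to them.

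Under Database Setup, Random Assignment, and Blinding, "We will use stratified randomisation so that numbers of participating dyads in the control and intervention groups will be balanced within each hospital". Hospital is not named in the model. Table 1 places the T1 assessment, including AQoL-8D, before random assignment.

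**The concern.** Because T1 precedes allocation, any baseline difference between arms arises by chance. A test of that difference says nothing about whether the variable predicts later AQoL-8D, and prognostic value is the reason to adjust. The covariates in the primary model are therefore set by the draw and cannot be known until the baseline data are in.

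The variable most likely to matter is the carer's own baseline AQoL-8D. Under the plan it enters only by subtraction, which forces its coefficient to 1. As a covariate its coefficient would be estimated, and the group difference would be more precise for any correlation below 1. At stake is power that the trial could have from data it already collects.

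This is not a detail left to a statistical analysis plan, because the protocol itself prescribes the selection rule.

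**Working it through.** **Inputs.** Effect size 0.22, 80% power and 324 per arm are from Power Calculations. The 0.05 level is from Statistical Analysis; sidedness is not stated. The correlation rho between baseline and follow-up AQoL-8D is not in the protocol and is assumed.

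**1. The plan's own figure.** n per arm = 2(1.960 + 0.842)²/0.22² = 324.3, which rounds up to 325. A t-based calculation gives 326. A one-sided test would need 256, so a two-sided test was used. Power at 324 per arm is 0.800 (normal) or 0.798 (t). The stated sample size reproduces and is not in dispute.

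**2. Variance.** Take one follow-up, with equal variance (set to 1) at baseline and follow-up.

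- Change score: variance 2(1 − rho).
- Baseline-adjusted: variance 1 − rho².
- Adjusted over change = (1 + rho)/2, so change over adjusted = 2/(1 + rho).

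The change-score variance is 33% larger at rho 0.5 (2/1.5), 18% at 0.7 (2/1.7) and 5% at 0.9 (2/1.9).

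**3. Power at 324 per arm, with 0.22 per SD of change.** Unadjusted, the expected test statistic is 0.22 × √(324/2) = 2.80. Dividing by √((1 + rho)/2) gives the adjusted value, and power is Φ(that value − 1.96).

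| rho (assumed) | (1+rho)/2 | Power, change score | Power, baseline always in model | n per arm for 80% |
|---|---|---|---|---|
| 0.3 | 0.65 | 0.80 | 0.935 | 211 |
| 0.5 | 0.75 | 0.80 | 0.899 | 244 |
| 0.7 | 0.85 | 0.80 | 0.859 | 276 |
| 0.9 | 0.95 | 0.80 | 0.819 | 309 |

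**4. Does the conditional rule recover the loss?** The rule was simulated for baseline AQoL-8D alone, reading an evident difference as p<0.05 (324 per arm, one follow-up, 20,000 runs per setting).

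| rho | Power, conditional rule | Power, always adjusted | Type I error, conditional rule |
|---|---|---|---|
| 0.5 | 0.806 | 0.898 | 0.040 |
| 0.7 | 0.807 | 0.861 | 0.045 |
| 0.8 | 0.802 | 0.838 | 0.047 |

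The rule triggers in about 5% of trials, so it recovers almost nothing. It does not inflate the type I error.

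**5. Hospital.** If hospital explains 1%, 2% or 5% of the variance (assumed), including it moves power from 0.800 to 0.804, 0.807 or 0.819.

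**The case against.** **Error rate.** A reader might infer that a model chosen after baseline tests inflates false positives. That is not supported. Selection depends on baseline imbalance and never on outcomes, the exported data carry only a group code so that the effectiveness analysis can be blinded, and the simulated error is slightly below nominal.

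**Regression to the mean.** A reader might also infer bias. Under randomisation it acts on both arms equally in expectation, so the change-score comparison is unbiased. A chance imbalance just short of significance would go uncorrected, but that is the same precision loss seen in a single trial, not a further fault.

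**Chance selection.** With 20 independent variables screened at 5%, at least one null variable enters with probability 1 − 0.95²⁰ = 64%; with 5 variables it is 23%. Neither the count nor the 5% threshold for an evident difference is in the protocol, and a null covariate among 648 carers costs almost nothing. The figure shows that selection is arbitrary and does not measure harm.

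**Scope of the power gain.** The formula is for a group difference at one time point. The protocol also plans a time-by-group interaction. A baseline main effect cancels from contrasts among the follow-ups, so adjustment does not sharpen that test in complete data. This stands. The gain belongs to the group difference in change, at a time point or averaged over follow-ups.

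**Meaning of 0.22.** The protocol does not say whether it is per SD of change or per SD of score. On the score scale at rho 0.7, power is already 0.951 unadjusted and 0.975 adjusted, so the practical loss would be small. At rho 0.3 on that scale it is 0.658 against 0.835. The direction is the same throughout; the size is uncertain.

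**Other adjustment.** The Data Linkage section foresees controlling for pre-baseline service use, but neither lists the variables nor ties them to the primary model. The missing hospital term alone could be left to a statistical analysis plan; it supports the point without carrying it.

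**Conclusion.** The point holds as one of efficiency and pre-specification. The protocol fixes a data-driven covariate rule that ignores prognostic value and uses baseline AQoL-8D only by subtraction unless the arms happen to differ on it. The analysis is valid and its sample size is adequate for an unadjusted change score if 0.22 is per SD of change.

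On that same reading, fixing baseline AQoL-8D in the model would raise power at 324 per arm from 0.80 to about 0.90, 0.86 or 0.82 for rho of 0.5, 0.7 or 0.9. These sizes rest on the assumed rho, equal variances at the two times and a single follow-up. That there is a gain, for any rho below 1, does not depend on how 0.22 is scaled. Hospital would be expected to add little.

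**What to change.** In the Statistical Analysis section of the protocol, and in the statistical analysis plan:

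- Delete the baseline significance tests and the rule that adds covariates when differences are evident. Present baseline data descriptively by arm.
- Name baseline AQoL-8D and hospital, the randomisation stratum, as fixed covariates in the primary model.
- For each continuous secondary outcome, name its own baseline value and hospital.

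The cost is wording, settled before analysis begins. No extra data are needed: Table 1 already collects these measures at T1 before allocation, and hospital is known for every dyad.
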